## Abstract

**Background:**

Coronary computed tomography angiography (CCTA) is an established method for ruling out coronary artery disease (CAD). Most patients referred for CCTA do not have CAD and only approximately 20–30 % of patients are subsequently referred to further testing by invasive coronary angiography (ICA) or non-invasive perfusion evaluation due to suspected obstructive CAD. In cases with severe calcifications, a discrepancy between CCTA and ICA often occurs, leading to the well-described, low-diagnostic specificity of CCTA. As ICA is cost consuming and involves a risk of complications, an optimized algorithm would be valuable and could decrease the number of ICAs that do not lead to revascularization.

The primary objective of the Dan-NICAD study is to determine the diagnostic accuracy of cardiac magnetic resonance imaging (CMRI) and myocardial perfusion scintigraphy (MPS) as secondary tests after a primary CCTA where CAD could not be ruled out. The secondary objective includes an evaluation of the diagnostic precision of an acoustic technology that analyses the sound of coronary blood flow. It may potentially provide better stratification prior to CCTA than clinical risk stratification scores alone.

**Methods/design:**

Dan-NICAD is a multi-centre, randomised, cross-sectional trial, which will include approximately 2,000 patients without known CAD, who were referred to CCTA due to a history of symptoms suggestive of CAD and a low-risk to intermediate-risk profile, as evaluated by a cardiologist. Patient interview, sound recordings, and blood samples are obtained in connection with the CCTA. All patients with suspected obstructive CAD by CCTA are randomised to either stress CMRI or stress MPS, followed by ICA with fractional flow reserve (FFR) measurements. Obstructive CAD is defined as an FFR below 0.80 or as high-grade stenosis (>90 % diameter stenosis) by visual assessment.

Diagnostic performance is evaluated as sensitivity, specificity, predictive values, likelihood ratios, and C statistics. Enrolment commenced in September 2014 and is expected to be complete in May 2016.

**Discussion:**

Dan-NICAD is designed to assess whether a secondary perfusion examination after CCTA could safely reduce the number of ICAs where revascularization is not required. The results are expected to add knowledge about the optimal algorithm for diagnosing CAD.

**Trial registration:**

Clinicaltrials.gov identifier, NCT02264717. Registered on 26 September 2014.

**Electronic supplementary material:**

The online version of this article (doi:10.1186/s13063-016-1388-z) contains supplementary material, which is available to authorized users.

## Background

An increasing number of patients are referred for evaluation of coronary artery disease (CAD) based on atypical symptoms. No unequivocal diagnostic strategy has been established for diagnosing CAD in patients presenting with symptoms suggestive of stable angina pectoris, and for that reason, clinical practice varies around the world.

The gold standard for detecting hemodynamic obstructive CAD is invasive coronary angiography (ICA) with fractional flow reserve (FFR) measurement [1–3]. However, ICA is costly and involves a small risk of complications and death [4]. Coronary computed tomography angiography (CCTA) has become an established procedure to examine patients with a low to intermediate risk of CAD [5–11]. Due to high negative predictive value, obstructive CAD can be excluded by CCTA in approximately 70–80 % of these patients [11], depending on the risk of the referred population. However, CCTA has consistently proven to have a low positive predictive value, often resulting in an overestimation of the severity of CAD [12], especially in patients with moderate to severe coronary calcification. Consequently, the introduction of CCTA has not led to a substantial decrease in the number of annually performed ICAs or increased the frequency of revascularisation procedures following ICA [13]. The above-mentioned issues raise the question of whether it is possible (1) to make a more precise risk stratification and consequently better selection of patients prior to CCTA and (2) to reduce the number of patients referred for unnecessary ICAs after CCTA.

European guidelines recommend conducting a myocardium perfusion examination after CCTA to reduce the number of ICAs when no revascularization is performed [14], although disagreement still exists regarding which perfusion examination to use.

Cardiac magnetic resonance imaging (CMRI) offers many advantages such as no radiation exposure and high image resolution [15–20]. A lack of scanner capacity and expertise are often mentioned as limitations. Myocardial perfusion scintigraphy (MPS) is an established perfusion test; however, disadvantages such as radiation and low sensitivity are reported as well as a balanced reduction in blood flow to the myocardium in three-vessel disease [21–24]. Many studies assessing the diagnostic accuracy of CMRI and MPS have used ICA diameter stenosis as a reference standard [16, 18[20, 22], which has been shown to be inaccurate in assessing the functional significance of a coronary stenosis compared to ICA-FFR [3].

A meta-analysis on MPS found an average sensitivity of 84 % for women and 89 % for men and a specificity of 78 % for women and 71 % for men using invasive coronary angiography– quantitative coronary angiography (ICA-QCA) as a reference standard [25]. For CMRI, a meta-analysis of studies performed with ICA-FFR as the reference found an average sensitivity of 90 % and a specificity of 87 % [17].

The CADScor System (Acarix A/S, Denmark) is a newly developed technology, which automatically analyses sounds from the heart and extracts multiple acoustic features related to turbulent blood flow, which emerges in a coronary segment with stenosis, and other heart sounds characteristic to CAD [26–29]. Based on these characteristics, the system calculates a score. This score can potentially be used for risk stratification prior to CCTA and in diagnosing CAD [29].

The first objective of the present study is to determine the precision of MPS and CMRI as secondary examinations after CCTA when significant stenosis cannot be excluded.

Our second objective is to examine the diagnostic precision of the CAD score in patients with a low to intermediate risk of CAD and who have been referred to a primary examination by CCTA.

## Methods/design

### Study design

Dan-NICAD is an investigator-initiated, multi-centre, randomised, cohort trial examining patients without known CAD, who have been referred to CCTA due to a history of symptoms suggestive of CAD. Study subjects are being recruited at two regional hospitals (Department of Cardiology, Regional Hospitals of Herning and Silkeborg, Denmark). Approximately 2,000 patients with low to intermediate risk of CAD will be included and possibly supplied if needed until a minimum of 300 patients have been randomised and completed perfusion imaging. It is expected that 1,000 patients will be enrolled at each site, as the two centres have similar annual activity in terms of performed CCTAs. Patients with a normal CCTA will not undergo further evaluation, whereas patients with suspected obstructive CAD on CCTA are being randomised. Randomisation is 1:1 for either CMRI or MPS, with subsequent ICA with FFR analysis in both arms. A patient flowchart is included in Fig. 1. All perfusion examinations will be conducted at the two regional hospitals, and the ICA with FFR will be conducted at the Aarhus University Hospital, Aarhus, Denmark. The cohort will be followed for clinical events for 10 years.

**Fig. 1 Fig1:**
[figure not shown]
Danish study of Non-Invasive testing in Coronary Artery Disease (Dan-NICAD) patient flowchart. CAD, coronary artery disease; CCTA, coronary computed tomography angiography; CMRI, cardiac magnetic resonance imaging; MPS, myocardial perfusion scintigraphy; ICA-FFR, invasive coronary angiography-fractional flow reserve

### Study population

The cohort consists of patients referred to CCTA with low or intermediate pre-test probability for CAD. The pre-test probability is based on a clinical assessment in an outpatient cardiology setting. Inclusion and exclusion criteria are listed in Table 1. In all enrolled patients, an acoustic examination with the CADScor® system is performed, an interview is conducted, and a blood sample is obtained and stored in a biobank.

**Table 1 Tab1:** Study enrolment criteria

Criteria for inclusion
- Patients with low intermediate pre-test risk of CAD, with an indication for CCTA
- Qualified patients who have signed a written informed consent form
Criteria for exclusion
- Age below 40
- Pregnant women, including women who are potentially pregnant or lactating
- Contra-indication for adenosine (severe asthma, advanced AV block, or critical aorta stenosis)
- Reduced kidney function, with an estimated glomerular filtration rate (eGFR) < 40 mL/min.
- Contra-indications for MRI
- Allergy to X-ray contrast medium
- Previous PCI, CABG, or POBA

*CAD* coronary artery disease, *CCTA* coronary computed tomography angiography, *MRI*, magnetic resonance imaging, *PCI* percutaneous coronary intervention, *CABG*: coronary artery bypass grafting, *POBA*: plain old balloon angioplasty

### Blood samples

Four blood samples will be collected from all patients before X-ray contrast medium is administered for the CCTA. These samples will be centrifuged, and for each patient, three 1-mL vials of serum, three 1-mL vials of ethylenediaminetetraacetic acid (EDTA) plasma, and three 1 mL vials of heparin plasma are being collected with the purpose of creating a biobank. In addition, the buffy coat layer from both the EDTA-buffered blood and the heparin-buffered blood are being collected and stored for the purpose of DNA and RNA isolation. All samples are being stored in a -80 °C freezer. The purpose of the biobank is to perform genetic analysis related to risk factors and identify new biomarkers associated with the development of arteriosclerosis. The details of these analyses are beyond the scope of this paper.

### CAD score

The acoustic heart score, which is the CAD score, is being measured in connection with the CCTA examination.

Heart sound recordings are obtained with the microphone from the CADScor system (Acarix A/S, Denmark) mounted at the 4th intercostal space just left to sternum using a dedicated patch. The patient has to lie down for 3 min during the recordings and will be asked to hold his/her breath four times for a duration of 7.5 s. As the equipment is sensitive to sounds coming from the outside, tests are conducted in an undisturbed room. Immediately afterward, the recording the equipment will automatically calculate a CAD score. The CAD score is estimated from a fully automated algorithm, which extracts multiple acoustic features from the diastolic heart sounds related to potential turbulence murmurs and other heart sounds characteristics related to CAD [26–29].

The CADScor system analyses the quality of the heart sound; in cases of poor recording quality e.g. a high level of ambient noise, the CADScor device will request a new recording. In these cases, a second attempt is being made to estimate the CAD score.

### Coronary computed tomography angiography (CCTA)

#### Patient preparation

Prior to CCTA, patients are asked to abstain from coffee, tea, and tobacco on the morning of the examination. Ahead of scanning, most patients will be asked to take 50–100 mg of metoprolol or 7.5 mg of ibravadin in order to obtain an optimal heart frequency below 65 beats per minute (BPM). Before imaging, patients with a heart rate higher than 65 BPM will be administered Seloken® (metoprolol tartrate 2.5–20 mg intravenous) if there are no contraindications. Prior to the CCTA, all patients receive 0.8 mg of sublingual nitroglycerin.

#### Imaging protocol

Scans are performed on a 320 multi-slice volume CT scanner (Aquillion One, Toshiba Medical Systems, Japan) using prospective electrocardiogram (ECG) gating.

After anteroposterior and lateral scanograms, a non-enhanced scan will be performed using prospective ECG triggering over a single heartbeat with a gantry rotation and x-ray exposure time of 0.35 s, 0.5-mm slice collimation, tube voltage of 120 kV, and the tube current automatically adjusted with a noise index 80 standard deviation (SD). The start and end positions are determined using the non-enhanced scan. To minimize radiation exposure, the range is reduced as much as possible. In most cases, z-axis coverage is 140 mm but may range from 120 to 160 mm, depending on the length of the heart. The CCTA protocol is performed using a peak tube voltage of 100 kV, except for obese patients where 120 kV is required, a gantry rotation time of 0.35 s, and prospective ECG triggering. 50–80 mL non-ionic contrast agent (Optiray 350 mg/mL, Mallinckrodt, Ireland) is administrated according to patient weight. Real-time bolus tracking is performed in the descending aorta and begins 5 s after the start of the contrast injection. Once a target threshold of 180 Hounsfield units (HU) is reached in the descending aorta, the CCTA will be initiated during the pursuing breath hold.

Data are typically reconstructed at 65–75 % of the RR interval, with supplemental reconstructions when needed. A built-in PhaseExact (Toshiba Medical Systems, Japan) transfers the best phase at slice thickness 0.5 mm to a workstation (Vitrea Advanced Workstation, Vital Images, Minnetonka, MN, USA).

#### Imaging analysis

An experienced cardiologist performs the analyses. An Agatston calcium score is calculated using dedicated software (Vitrea Advanced Workstation, Vital Images, Minnetonka, MN, USA). Luminal diameter stenosis is evaluated in each segment of the coronary tree using the 18-segment model of the Society of Cardiovascular Computed Tomography [9]. Coronary lesions are quantified by visual assessment, and severity is classified as follows: no stenosis—0 % diameter reduction (*≈* 0 % area reduction); mild stenosis—1 to 29 % diameter reduction (*≈* 1 to 50 % area reduction); moderate stenosis—30 to 49 % diameter reduction (*≈* 50 to 69 % area reduction); and severe stenosis—50 to 100 % diameter reduction (*≈* 70 to 100 % area reduction). Severe stenosis and non-evaluable segments with a diameter greater than 2 mm are defined as having obstructive CAD. CCTA is defined as abnormal if obstructive CAD cannot be ruled out in all coronary segments.

### Myocardial perfusion scintigraphy (MPS)

#### Preparation

The patients are advised to abstain from caffeine (coffee, tea, chocolate, and caffeinated medications) 24 h prior to the examination. If possible, patients treated with betablockers are asked to discontinue the treatment 48 h prior to the stress test.

#### MPS protocol

The preferred stress test is a standard symptom-limited exercise test on a bicycle (25 watt/2 min). If the patients are unable to perform an exercise test or if discontinuation of betablocker is contraindicated, a standard adenosine stress test (6-min infusion of 140 μg/kg/min) is performed. If adenosine is contraindicated (allergic asthma or severe COLD defined as a FEV1 < 50 % of expected), patients will be stressed with dobutamine. Tc99m-Sestamibi (10 MBq per kilogram of body weight) is injected at peak exercise or after 3 min of the adenosine infusion, when the target heart rate (= (220 - age) * 0.85) has been reached during the dobutamine infusion. Independent of the stress modality, the heart rate, blood pressure, and ECG are monitored throughout the test.

If the stress images are completely normal, no additional rest study will be performed. If the stress images reveal any suspicion of a perfusion or motion abnormality, a standard rest test (½ h of supine rest followed by injection of 10 MBq Tc99m-Sestamibi per kilogram of body weight) is conducted within 2 weeks.

#### MPS image acquisition

MPS is obtained in the supine position using a dedicated gamma camera (Cardio MD, Phillips Healthcare, Best, Holland) equipped with LEHR collimators and Vantage TM Gadolinium-153 line sources. A step-and-shoot acquisition in 64 projections, 20 s per emission projection, using a 180-degree RAO-LPO orbit and gating in eight frames, is applied. The transmission and emission images are obtained simultaneously. The duration of the transmission scan determines the scan acquisition time based on the Gd-153 source strength; i.e. 20 s per frame for new attenuation correction-sources, increasing to 25 s per frame for older sources (to ensure enough counts in AC image). The energy window is set at 140 keV ± 10 % for the acquisition of the emission images and at 100 keV ± 10 % for the acquisition of the transmission images. An additional 118 keV ± 6 % photopeak window is used to compensate for downscatter of Tc-99 m into the Gd-153 energy window.

After the stress acquisition, a nuclear technician reconstructs the images (see details below), and a nuclear medical physician decides if the patient should undergo a rest test. The raw projection data from the stress and the possible rest acquisitions are stored digitally.

The stress images are obtained within 1 hour after the Tc injection if stress is performed with exercise or adenosine-low exercise and within 3 h after supine adenosine stress or dobutamine stress. The rest images are acquired within 3 h after the injection.

#### Image reconstruction

After obtaining images, the raw image files will be de-identified and processed by an experienced nuclear medical physician using dedicated customized software [30] Cedar Sinai AutoSPECT 3.5 in Phillips Intellispace Portal v6.0.3.12200. An iterative maximum likelihood estimation method algorithm (12 iterations) starting out with a filtered back projection and using a Butterworth analytic filter with a cut off of 0.5 and order of 5.0 will be applied. Motion correction is added if the successive projections move more than 1 pixel in the y axis. Transmission data will be reconstructed similarly except for the use of a cut off of 0.6 and an order of 1.0. After the reconstruction, the left ventricle will be reoriented in short, vertical, and horizontal long axes, and these images will be saved for analysis.

#### Image analysis

Image analysis will be conducted in Cedar Sinai AutoQuant software in Phillips Intellispace Portal v6.0.3.12200 in an independent core lab by the same nuclear physician, who is blinded to additional patient information and results. The quality of the stress and rest images will be evaluated semi-quantitatively on a visual scale from 1 to 3. Scores defined as 1 represent a good image quality with no artifacts; scores defined as 2 indicate moderate image quality, acceptable for clinical or research diagnosis; and scores defined as 3 are consistent with poor image quality, and diagnosing is impossible due to severe artifacts. The MPS images are assessed using a 17-segment model. For each segment, perfusion defects are scored automatically by the software and adjusted visually on a five-point scoring system (0 is normal, and 4 is the absence of tracer uptake). The scores from the stress and rest images are summed, and a summed stress score (SSS), summed rest score (SRS), and summed difference score (SDS) will be produced. The images will also be evaluated qualitatively with a binary outcome (normal/abnormal). An abnormal MPS scan is defined as (1) an SDS ≥ 43? involving ≥ 2 contiguous segments corresponding to approximately 10 % (reversible ischemia); (2) an SRS ≥ 43? involving ≥ 2 contiguous segments (irreversible ischemia); (3) a combination of reversible and irreversible ischemia involving ≥ 2 contiguous segments (mixed ischemia). Poor image quality (score 3, non-diagnostic) is considered abnormal (Fig. 2).

**Fig. 2 Fig2:**
[figure not shown]
Perfusion defect on myocardial perfusion scintigraphy. Myocardial perfusion scintigraphy with Tc-99 m Sestamibi: short-axis and horizontal long-axis images during stress (upper rows) and rest (lower rows). A severe reversible perfusion defect is seen in the anteroseptal area of the left ventricle

A hybrid imaging analysis, combined with information from the CCTA and MPS, blinded from the result of the ICA, is performed after the initial analysis.

### Cardiac magnetic resonance imaging (CMRI)

#### Patient preparation and imaging hardware

Patients are advised to abstain from eating at least 2 h before scanning to avoid adverse side effects of the adenosine, which include nausea and vomiting. Patients are also advised to abstain from caffeine 24 h prior to the examination. The CMRI scans will be conducted using two identical 1.5 Tesla systems (Siemens MAGNETOM Avanto, Software release VB17A, Siemens Healthcare GmbH, Germany) using a dedicated 32-channel cardiac-receiver coil. Blood pressure, distal oxygen saturation, and a vector ECG will be monitored continuously during the examinations using a MedRad® Veris® monitoring system (Bayer Healthcare LCC, Berkeley, CA, USA).

All sequences are ECG gated, whereas motion artifacts are minimized by breath-holding and navigator gating. The total scan time is approximately 50 min, which includes patient preparation, scanner set-up, and imaging.

A series of CMRI scans are included to enable the assessment of information on cardiac morphology, function, perfusion, and viability state of the myocardium

#### Imaging protocol

Cardiac morphology is evaluated from axial and sagittal two-dimensional (2D) image series covering the entire heart using a navigator gated single-shot echo-planar fast spin echo sequence (HASTE: Half-Fourier Acquisition Single-shot Turbo spin-Echo) [31] (spatial resolution = 1.9 × 1.3 mm^2^, slice thickness = 8 mm, FOV = 340 mm, TR = 800 ms, TE = 26 ms, Matrix size = 256, flip angle = 160°, Partial Fourier = 5/8, Number of echoes = 123, Time between echoes = 3 ms, and Bandwidth = 698Hz/pixel).

Left ventricular function is evaluated using a time-resolved (cine) 2D balanced Steady State Free Precession (TrueFISP: True Fast Imaging with Steady-state Precession) [32, 33] sequence in which slice planes were acquired yielding four-chamber, three-chamber, and two-chamber views; short-axis views; and an image of the left ventricular outflow tract (LVOT) (spatial resolution = 1.8–2.4 × 1.2–1.6 mm^2^, slice thickness = 8 mm, FOV = 300–400 mm, TR = 201–223 ms, TE = 1.14–1.27 ms, Matrix size = 256, flip angle = 80°, GRAPPA = 3, Bandwidth = 1149 Hz/pixel).

Rest and stress perfusion imaging are performed using an ECG-triggered, contrast-enhanced, dynamic, 2D, gradient, echo, Fast Low Angle Shot (TurboFlash) [34] sequence in three short axis slice planes (basis, mid, and apex) (spatial resolution = 2.4 × 2.1 mm^2^, slice thickness = 10 mm, FOV = 330 mm, TR = 201 ms, TE = 1.05 ms, TI = 130 ms, Matrix size = 160, flip angle = 10°, Partial Fourier = 7/8, GRAPPA = 2, and Bandwidth = 651Hz/pixel). (Fig. 3)

**Fig. 3 Fig3:**
[figure not shown]
Perfusion defect on coronary magnetic resonance imaging. Coronary magnetic resonance imaging during pharmacological stress induced hyperemia (**a**) and at rest (**b**). The patient has an anteroseptal and lateral reversible perfusion defect in the midcardial segments of the left ventricle

Stress perfusion imaging is carried out after an intravenous bolus injection of either 5 mL of Regadenoson (Lexiscan, Astellas Pharma, USA) or following intravenous adenosine-induced hyperemia. Adenosine is infused for 6 min at 140 μg/kg/min. In case of an inadequate peripheral haemodynamic response to standard dose (an increase in heart rate of more than 10 beats per minute, a systolic blood pressure drop of more than 10 mmHg from baseline or no symptoms), the adenosine infusion is increased to 170 μg/kg/min or even 210 μg/kg/min, depending on the patient response. Independently of the pharmacological stress approach (Regadenoson or adenosine), an intravenous bolus of Gadovist® (Bayer Schering Pharma AG, Germany) or Dotarem® (GD-DOTA, Guerbet LCC, USA) with a concentration of 0.5–0.1 mmol/kg will be administered at a flow rate of 4.0 mL/s through the left cubital vein using a 18 G syringe followed by a 20 mL saline flush (Medrad® Spectris Solaris® power injector, Bayer Healthcare LCC, USA).

Rest perfusion scans are performed after pharmacological stress washout using the same sequence parameters and dose of contrast agent as for the stress perfusion.

Viability evaluation of the myocardium is carried out using a 2D single shot TrueFISP Phase Sensitive Inversion Recovery (PSIR) [35] sequence in the short axis plane of the heart (spatial resolution = 1.8 × 1.8 mm^2^, slice thickness = 8 mm, FOV = 340 mm, TR = 700 ms, TE = 1.09 ms, TI = 300 ms, Matrix size = 192, flip angle = 40°, GRAPPA = 2, Bandwidth = 1447Hz/pixel). The images are acquired approximately 10 min after contrast injection to insure optimal contrast enhancement.

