#### Imaging protocol

All stenoses are visually assessed, and all stenoses above 30 % in vessels with a reference diameter above 2 mm are examined, with at least two projections at least 30 degrees apart revolving around the axis of the vessels. The overlap of vessels is avoided if possible. Angiography is recorded at a time resolution of 15 frames per second (fps).

FFR measurements are performed in all coronary segments with a diameter > 2 mm where ICA shows the presence of stenosis with a diameter ≥ 30 % by visual assessment. The position of the FFR wire is documented angiographically. FFR is measured using a pressure wire (Aeris, St. Jude Medical, Minnetonka, MN, USA) during continuous recording of the pressure curves. Hyperaemia is induced by an intravenous adenosine infusion of a 1 mg/mL concentration of adenosine at 140 μg/L/min. The infusion rate is increased to 200 μg/L/min if a stable FFR value is not achieved. Routine checks are made to ensure that ‘drift’ does not occur after FFR recordings. If the drift value exceeds 1.04 or is below 0.96, the FFR-measurement is repeated. Furthermore, all severe stenoses (> 90 %) in vessels with a reference diameter above 2 mm where there is no immediate indication of treatment, FFR is not possible or not attempted, are noted.

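### The CMRI rule for raising adenosine after an inadequate response lists two signs that the patient has responded

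*Protocol article*

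**What the plan says.** The rule is in the Protocol article under Cardiac magnetic resonance imaging (CMRI), Imaging protocol, in the text after the Fig. 3 caption. Stress is induced with a regadenoson bolus or with adenosine. For adenosine the standard regimen is: "Adenosine is infused for 6 min at 140" μg/kg/min.

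The escalation condition opens "In case of an inadequate peripheral haemodynamic response to standard dose (an increase in heart rate of more than 10 beats per minute" and its parenthesis continues "a systolic blood pressure drop of more than 10 mmHg from baseline or no symptoms". The action follows: "the adenosine infusion is increased to 170" μg/kg/min, or even to 210, according to how the patient responds.

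Two other places bear on the point:

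- CMRI, Patient preparation and imaging hardware: "Blood pressure, distal oxygen saturation, and a vector ECG will be monitored continuously during the examinations".
- ICA-FFR examination, Imaging protocol: a separate adenosine rule, under which the infusion rate is raised "if a stable FFR value is not achieved".

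**The concern.** A parenthesis placed directly after a condition is normally read as its definition. Here the condition is a response that falls short, yet two of the three defining items are evidence that a response has occurred. The third, absence of symptoms, points the other way.

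Anyone applying the printed cut-offs would increase the infusion in patients who already show the wanted haemodynamic change. They would also leave the dose unchanged in a patient who reports symptoms but has no change in heart rate or pressure. Two things are at stake: unnecessary exposure to a higher dose of a vasoactive drug, and adequate, uniform stress in the CMRI examination, one of the two index tests in the first objective. The sample size, the analysis and the reference standard are not affected.

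**Working it through.** The plan gives no figure to reproduce. The check is to classify the items and then list what the printed rule does.

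**Step 1: direction of each item.**

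| Item in the parenthesis | What it indicates | Fits an inadequate response? |
|---|---|---|
| Heart-rate rise of more than 10 bpm | Response present | No |
| Systolic drop of more than 10 mmHg | Response present | No |
| No symptoms | Response absent | Yes |

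If the list defines an inadequate response, items 1 and 2 are the wrong way round. If it describes the wanted response, item 3 is the wrong way round. Neither reading makes the three consistent.

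**Step 2: what the rule does.** Let H = heart-rate rise above 10 bpm, S = systolic drop above 10 mmHg, Y = symptoms present. There are 2 × 2 × 2 = 8 combinations. Three rules are compared:

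- Printed: escalate if H, or S, or not Y.
- Corrected, all signs missing (*and*): escalate if not H and not S and not Y.
- Corrected, any sign missing (*or*): escalate if not H, or not S, or not Y.

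| H | S | Y | Printed | Corrected, *and* | Corrected, *or* |
|---|---|---|---|---|---|
| no | no | no | raise | raise | raise |
| no | no | yes | hold | hold | raise |
| no | yes | no | raise | hold | raise |
| no | yes | yes | raise | hold | raise |
| yes | no | no | raise | hold | raise |
| yes | no | yes | raise | hold | raise |
| yes | yes | no | raise | hold | raise |
| yes | yes | yes | raise | hold | hold |

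- The printed rule escalates in 7 of 8 combinations.
- Against the *and* rule it wrongly escalates 6 and wrongly withholds 0.
- Against the *or* rule it wrongly escalates 1 (full responder) and wrongly withholds 1 (symptoms only).
- The two corrected rules differ from each other in 6 of 8.
- Under both corrections the full responder in the last row is wrongly escalated.

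**Step 3: size of the dose change.** 170/140 − 1 = 0.214, or 21 %; 210/140 − 1 = 0.50, or 50 %.

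**Step 4: who is concerned.** Only CMRI patients stressed with adenosine. The Study design section gives a minimum of 300 patients randomised 1:1, so 300/2 = 150 in the CMRI arm at that minimum. The adenosine share is not stated.

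**Step 5: is it an extraction fault?** The sentence is complete and the comparator is spelled out in words, so a lost inequality sign cannot explain it.

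**The case against.** The strongest reply is that the sentence is clear without its parenthesis. It opens with an inadequate response and ends by titrating to the patient's response, so a clinician would not treat a heart-rate rise as a failure to respond. The first two items may also be meant to explain the word *response*, with only the mention of symptoms misplaced; both 10-unit cut-offs would then be correct as markers of response. The article condenses a fuller protocol, patients were already being scanned when it was written, and nothing suggests that scanner staff titrate from this sentence. Patients with contraindications to adenosine are excluded, and monitoring is continuous. The figure of 150 is a planned minimum: 226 randomised of 1,100 enrolled is 20.5 %, which over 2,000 gives about 411 patients, or about 205 per arm.

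Much of this stands. The intent is recognisable, harm is not shown, the ICA-FFR rule is only loosely analogous because it concerns a stable FFR reading, and the combination counts say nothing about how many patients fall in each row.

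It does not rescue the text. The alternative reading still leaves one item contradicting the other two. It also matters for the repair: if the list describes a response shown by any one sign, its negation is the *and* rule, whereas negating each item and keeping the printed connective gives the *or* rule. A careful reader can guess the direction but cannot recover the rule. Monitoring supplies the readings; it does not correct the printed cut-offs for acting on them.

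**Conclusion.** The point holds: the escalation criterion is wrong as written and is corrected nowhere else in the article. Applied literally, it would raise the dose in full responders by 21 % or 50 %, whichever corrected rule was intended. Its wider effect depends on the intended connective: from 1 combination wrongly escalated and 1 wrongly withheld (*or*) to 6 wrongly escalated and none withheld (*and*). These are logical combinations, not patients. The number of patients concerned is an unknown share of about 150 in the CMRI arm at the planned minimum, and more if recruitment runs above it.

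The conclusion assumes only that a heart-rate rise and a pressure drop are signs of response to adenosine, which the sentence's own label implies. It is most probably a drafting slip. It should be fixed because it is an operative dose threshold, but it gives no ground for doubting the trial's comparison.

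**What to change.** Reword the parenthesis so that all three items describe a missing response: heart-rate increase of not more than 10 bpm, systolic drop of not more than 10 mmHg from baseline, no symptoms. The clinical team should state explicitly whether escalation needs all three or any one of them; proofreading alone cannot settle this. Then confirm that the CMRI procedure in use at both hospitals matches the corrected sentence.

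The cost is one sentence and one check of the site procedure. Nothing in the sample size, analysis or data collection changes.
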